### 2.3. Randomization

Participants will be assigned to study arms after completion of the baseline enrollment survey. The study staff who enrolls each participant will notify the study biostatistician, who will provide the allocation. Randomization will be conducted using a computer-generated, permuted block randomization sequence stratified by dyad type (with or without mild AD/ADRD). Within each stratum, randomization will be performed using permuted blocks of 4 to ensure balanced group sizes. Both members of the dyad will be randomized together to the same intervention or control arm. The randomization sequence will be generated in advance by the study biostatistician using a random number generator and securely maintained within the study database, accessible only after baseline data collection is completed. After the third week of intervention, we will have a one-week crossover period, and all participants will switch to the alternate study arm. This one-week crossover period is a washout period to minimize the effects of promptings and motivations produced by the text messages, rather than to eliminate retained knowledge or behavior change. Group assignments will remain linked to each participant’s unique study ID throughout the study. The analyst will remain blinded to group assignments until data cleaning, feasibility, and preliminary efficacy analyses are complete.

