### 2.7. Study Procedure

The study will run for 10 weeks (Figure 2), starting with a one-week pre-intervention phase, followed by three weeks of intervention (or control), one week crossover phase, three weeks of control (or intervention), and a two-week post-intervention phase. The 3-week intervention period was selected to balance feasibility assessment with participant burden, consistent with pilot study methodology [39,40]. This duration provides adequate time to evaluate key feasibility outcomes while generating preliminary effect estimates to inform sample-size calculations for a definitive trial. Prior digital health intervention pilots have used a similar intervention period to assess the feasibility of technology-based interventions [41,42,43].

Week 1 (Pre-Intervention): The study team will call the dyad to confirm receipt of the study materials and ensure: (1) the appropriate wearing of the Fitbit smartwatches and data capture, (2) receipt of motivational text messages, and (3) access to the educational videos (Table 2). Data collected during this week will not be used for the study.

Weeks 2–4 (Phase I Intervention/Control): The intervention will start with dyads randomized to the intervention arms. Remote tracking of physical activity data will continue in the control arm.

Week 5 (Crossover/Washout): Participants will switch arms (intervention to control and vice versa). Activity data during this crossover week will not be analyzed (Table 2). Participants in the intervention arm will complete six post-intervention surveys (discussed below), and a few will participate in interviews.

Weeks 6–8 (Phase II Intervention/Control): Participants will continue in their new assignments (opposite of initial condition).

Weeks 9–10 (Post-Intervention): Crossover participants in the intervention arm will undergo post-intervention surveys and interviews. All participants will have access to the educational videos and video-guided physical rehabilitation sessions upon completion of the study (Table 2).

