where *Y_idt_* = outcome, *β*_0_ = fixed intercept, *Trt_i_* = treatment indicator, *Seq_i_* = sequence indicator, *Y_id_*_0_ = baseline value of the outcome, *Demi* = dementia status, *Trt × Dem* = treatment-by-dementia interaction, *Trt × Period =* treatment-by-crossover interaction, γ^⊤^*X_i_* = coefficient of covariates, and *b_d_* and *b_i(d)_* are the random intercept for dyad and individual nested within dyad, respectively. Treatment condition (intervention vs. control) and sequence (intervention-first vs. intervention-second) will be included as fixed effects to estimate the average intervention effect and to account for between-participant differences related to assignment order, respectively. Time will be modeled as a continuous weekly measure to capture trends over the six-week follow-up. Period will be modeled separately as a categorical indicator of pre- versus post-crossover phase to distinguish underlying activity trajectories from changes associated with withdrawal of active intervention components. Given the anticipated persistence of learning effects due to the short one-week washout period, the treatment × period interaction will be used to characterize maintenance or attenuation of intervention effects rather than to assume their absence. All analytical models will follow the intention-to-treat principle, and effect sizes with 95% confidence intervals will be reported to inform power calculations for a future definitive trial.

Qualitative Assessment: Semi-structured interviews will be conducted with dyads after completing the intervention phases. Dyads initially randomized to the intervention arm will be interviewed at crossover, while those starting in the control arm will be interviewed after completing the delayed intervention. Interviews will explore barriers and facilitators to smartwatch use, motivational texts, instructional educational modules, engaging in video-guided physical rehabilitation, walking exercise, and co-participating with a care partner. While we estimate conducting 10 to 20 interviews each for those with and without mild AD/ADRD, the exact number will be guided by the achievement of thematic saturation [68,69].

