**Figure 2 jcm-15-01341-f002:**
[figure not shown]
Timeline and schedule of enrollment, interventions, and assessments. A: Activity Tracking; B: Baseline Survey; C: Crossover Period; P: Post-Intervention Survey; I: Interviews; W: Week; X: Point where event occurs.

**Table 1 jcm-15-01341-t001:** Components of the ACTIVE Intervention.

Activity Tracking, Care Partner Co-Participation, Text Reminders, Instructional Education, Video-Guided Physical Rehabilitation, and Exercise	
Component	What It Includes
Activity Tracking	Fitbit Inspire 3 wearable, continuous step count and activity intensity monitoring, synced weekly
Care Partner Co-Participation	Care partner joining to supervise for safety and engage in home exercise, provide encouragement, and assist with technology
Text Reminders	Automated daily motivational text messages tailored to preceding day’s activity
Instructional Education	Digital education modules (short videos + PDFs): safe exercise, fall prevention
Video-Guided Physical Rehabilitation	Scheduled remote PT via video platform: Week 1: three sessions (gait, balance, strength) Weeks 2–4: weekly check-ins with progression Tailored exercise plans provided electronically
Exercise	Daily walking goal (≥15 min), tracked with wearable; progressive increase based on baseline activity

**Table 2 jcm-15-01341-t002:** Summary of the weekly schedule of the ACTIVE Intervention.

Time Point	Dyad Roles
Weeks 1: Pre-intervention	Control + Intervention Dyad: Mailing of printed educational infographics and smartwatch Troubleshooting to ensure data capture
Weeks 2–4	Control + Intervention Dyad: 1. Weekly dyad telephone check-in by research staff 2. Continuous tracking of activity Intervention Dyad Alone: 3. Two-weekly 3 min educational videos 4. Three-weekly video-guided physical rehabilitation schedule 5. Daily motivational texts
Week 5: Cross-over	Switch roles Interviews and Surveys Troubleshooting to ensure data capture
Weeks 6–8	Control + Intervention Dyad: 1. Weekly dyad telephone check-in by research staff 2. Continuous tracking of activity Control Dyad Alone: 3. Two-weekly 3 min educational videos 4. Three-weekly video-guided physical rehabilitation schedule 5. Daily motivational texts
Week 9–10	Interviews and Surveys

ACTIVE: Activity tracking, Care partner co-participation, Text reminders, Instructional education, Video-Guided Physical Rehabilitation, and Exercise—walking.

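### Week-5 activity data are barred from analysis, and the treatment × period term given the maintenance question instead cannot answer it from weeks 2–4 and 6–8

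*Protocol article*

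**What the plan says.** Section 2.7 rules out any use of the week-5 watch data: "Activity data during this crossover week will not be analyzed (Table 2". The data will nevertheless exist. Table 1 describes "continuous step count and activity intensity monitoring, synced weekly", and the week-5 row of Table 2 reads "Switch roles Interviews and Surveys Troubleshooting to ensure data capture".

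Section 2.3 gives the week its purpose: "This one-week crossover period is a washout period to minimize the effects of promptings and motivations produced by the text messages". It adds that retained knowledge and changed behaviour are not meant to be washed out.

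In Table 2 the active components for the dyads that began as controls appear under weeks 6–8: "Continuous tracking of activity Control Dyad Alone: 3. Two-weekly 3 min educational videos". Section 2.7 says of those weeks: "Participants will continue in their new assignments (opposite of initial condition". Under week 5, however, the same section says "Participants will switch arms (intervention to control and vice versa".

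Section 2.13 expects learning effects to persist past the short washout and says that the treatment × period "interaction will be used to characterize maintenance or attenuation of intervention effects rather than to assume their absence". Equation (6) also contains a sequence term. The effect size itself comes from the pre-crossover phase through Equation (5).

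**The concern.** The plan poses a question (what remains of the effect after the active components stop), assigns it to one model term, and excludes the data closest to it.

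On the Table 2 schedule, intervention-first dyads in week 5 have stopped and control-first dyads have not started. From week 6 every comparison group is on treatment, so no untreated concurrent group remains. The weeks 6–8 contrast is the delayed-start effect minus whatever persists in the withdrawn dyads, and one number cannot yield both.

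The stake is limited to the maintenance and carryover reading, but that reading is meant to help plan the definitive trial. A near-zero interaction could be reported as no carryover when there is some. As Equation (6) is written, software would either drop a term or return an arbitrary split between Seq and Trt×Period.

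**Working it through.** **The plan's own figure.** Section 2.8: √(0.75 × 0.25 / 100) = 0.0433; design effect 1 + (2 − 1) × 0.2 = 1.2; adjusted SE 0.0433 × √1.2 = 0.0474; 95% CI 0.657 to 0.843. This agrees with the stated 0.66–0.84. The present point does not depend on it, but the ICC of 0.2 is borrowed below.

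**Step 1: who is on what (Table 2 schedule).**

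| Weeks | Intervention-first (Seq = 1) | Control-first (Seq = 0) |
|---|---|---|
| 2–4 | on treatment | not yet treated |
| 5 | withdrawn | not yet treated |
| 6–8 | withdrawn | on treatment |

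**Step 2: aliasing in Equation (6).** Code Period 0 for weeks 2–4 and 1 for weeks 6–8.
- Weeks 2–4: Trt = Seq, so Trt + Period − 2·Trt×Period = Seq + 0 − 0 = Seq.
- Weeks 6–8: Trt = 1 − Seq, so the same sum is (1 − Seq) + 1 − 2(1 − Seq) = Seq.

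The identity holds in every row. A numerical check of the columns intercept, Trt, Seq, Time, Period, Dem, Trt×Dem and Trt×Period gives rank 7 with 8 columns. Random intercepts and further covariates do not remove this dependency.

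**Step 3: dropping Seq.** The matrix then has full rank (7 of 7). Let δ1 be the phase I effect, δ2 the delayed-start effect and λ the carryover in weeks 6–8.
- Phase I contrast, treated minus control: δ1.
- Phase II contrast, treated minus withdrawn: δ2 − λ.
- Trt×Period = (δ2 − λ) − δ1.

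Illustration with assumed values: δ1 = 0.40, δ2 = 0.60, λ = 0.20 SD gives (0.60 − 0.20) − 0.40 = 0, although half the phase I effect persisted. The values are chosen to cancel; they show that the term can mislead, not that it will. More generally, a model with week effects, treatment, treatment × period and carryover, and no sequence effect, has rank 8 of 9 on weeks 2–4 and 6–8. Neither the interaction nor carryover is estimable.

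**Step 4: what week 5 adds.** With week 5 included and no sequence effect (which randomisation supports), treatment, treatment × period and a carryover common to weeks 5–8 are all estimable (rank 10 of 10). If carryover may differ between week 5 and weeks 6–8, only the week-5 carryover is estimable.

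Putting week 5 into Equation (6) itself (Trt = 0 in both sequences, Period = post) restores rank 8 of 8. But the week-5 difference between sequences would then equal the Seq coefficient, so persistence would be labelled a sequence effect.

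**Step 5: precision of the week-5 contrast.** Inputs: 50 dyads and blocks of 4, so about 25 per sequence; ICC 0.1–0.3 (section 2.8, assumed to apply to activity); both members pooled; outcome SD not given, so results are in SD units.

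Half-width = 1.96 × √(2 × [(1 + ICC)/2] / dyads per sequence).
- 25 per sequence, ICC 0.2: 1.96 × √(2 × 0.6 / 25) = 1.96 × 0.219 = 0.43 (0.41 to 0.45 for ICC 0.1–0.3).
- At the 75% retention target, 0.75 × 25 = 18.75 per sequence: 1.96 × √(1.2 / 18.75) = 1.96 × 0.253 = 0.50 (0.48 to 0.52).

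**Step 6: baseline adjustment.** Multiplying 0.43 by √(1 − r²) with an assumed r of 0.6 to 0.7 would give 0.34 to 0.31. But watches are sent out after enrollment (section 2.2), and section 2.7 says week-1 data will not be used. No pre-treatment activity value is therefore available under the plan as written, although Equations (5) and (6) both contain one.

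**The case against.** Leaving washout data out of a treatment-effect model is ordinary practice. The effect size comes from pre-crossover data, maintenance is not one of the two stated aims, the trial is a feasibility pilot not powered for efficacy, and the Discussion declares carryover as a limitation. All of that stands, and it limits the consequence.

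The week-5 contrast is also imprecise. With an assumed carryover of 0.20 SD the expected interval is 0.20 ± 0.43, or −0.23 to 0.63. It would cover both no carryover and full persistence of a 0.40 effect. That stands too; it argues for descriptive reporting with an interval, not for barring the data.

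A reader might infer three stronger things that the documents do not support.
- *That week 5 gives an unconfounded measure of carryover.* In that week only the dyads finishing the intervention complete post-intervention surveys, and a few are interviewed (sections 2.7 and 2.12), which may prompt activity in one sequence. The week-5 arm-switch wording also leaves unclear whether control-first dyads are wholly untreated then.
- *That week 5 settles maintenance.* It shows the first week off only, and only for activity metrics, since no week-5 survey is taken in the control-first dyads. Carryover in weeks 6–8 may differ.
- *That baseline adjustment would bring the interval near ±0.3 SD.* That needs watch data which the plan excludes.

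**Conclusion.** The point holds in a limited form. Section 2.7 excludes data that will be captured anyway and that hold the only concurrent randomised comparison of withdrawn with not-yet-treated dyads. The term given the maintenance question is not estimable in Equation (6) as written, and without Seq it cannot separate carryover from a treatment effect that differs between phases. These two statements about Equation (6) are exact algebra.

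The value of week 5 rests on assumptions: that the Table 2 schedule applies, so control-first dyads are untreated that week; that there is no true sequence effect; and that the one-sided surveys and interviews have little influence. Expected precision is about ±0.43 SD, or ±0.50 SD if only 75% of dyads remain, without baseline adjustment. The pre-crossover estimate and the feasibility outcomes are untouched. The change is worth making because it is cheap and serves a question that the plan itself raises; the trial does not depend on it.

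**What to change.** 1. Replace the exclusion sentence in section 2.7 with, for example: *Week-5 activity data are excluded from the treatment-effect models. The week-5 difference between sequences (intervention-first minus control-first) in each activity metric will be reported descriptively with a 95% CI, adjusted for AD/ADRD stratum with a dyad random intercept, beside the phase I effect, as first-week persistence only.*
2. Decide whether week-1 watch data may serve as the baseline activity value. Adjust the week-5 contrast for it only if so, and align section 2.7 with the baseline term in Equations (5) and (6). Otherwise state the expected unadjusted precision.
3. State that week-5 surveys and interviews take place in the intervention-first sequence only, and add a sensitivity analysis restricted to days before them.
4. Reconcile the week-5 arm-switch wording in section 2.7 with the washout in section 2.3 and the weeks 6–8 start in Table 2. The contrast can be interpreted as above only if the reconciled text leaves control-first dyads untreated in week 5.
5. Do not include both Seq and Trt×Period in Equation (6), and do not interpret Trt×Period alone as maintenance or attenuation. Adding week 5 to that equation is not the remedy.

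Cost: a few sentences and one extra model on data already captured. The downsides are a wide interval and fewer usable days in the sensitivity analysis.

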### 2.8. Sample Size Determination

For this pilot study, the trial is not powered to detect clinical efficacy but to provide adequate precision for estimating feasibility metrics and to inform the design of a future fully powered effectiveness–implementation trial [44]. We will enroll 50 dyads (older adult + care partner), a recommended sample size for behavioral pilot trials and digitally delivered rehabilitation interventions [44,45,46]. A sample of 50 dyads (n = 100) provides adequate precision to estimate key feasibility parameters that guide go/no-go decisions.

For a feasibility outcome, the unadjusted standard error (SE), assuming independence, is estimated using the formula in Equation (1). Using an expected proportion of 0.75 (e.g., completion of ≥75% of virtual PT modules), the unadjusted SE is 0.043.(1)SE=p (1−p)n

To account for dyadic clustering, we assume an intra-cluster correlation (ICC) of 0.1–0.3, which is typical for partner dyads [47,48]. Using the design effect formula in Equation (2), an ICC of 0.2, and a cluster size (m) of 2, the design effect is 1.2, and the cluster-adjusted SE (Equation (3)) is 0.047. The cluster-adjusted 95% CI for a 75% completion rate (Equation (4)) is therefore 0.66–0.84.Design Effect = 1 + (m − 1) × ICC(2)Cluster-adjusted Standard Error (adjusted SE) = Unadjusted SE × √(Design Effect)(3)(4)95% CI=p±1.96×adjusted SE

This level of precision is appropriate for feasibility-focused pilot research, where the goal is to estimate plausible ranges and plan thresholds for an adequately powered future trial.

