Text reminders: Validated motivational text messages will be delivered to both care recipients and care partners at scheduled morning times tailored to each dyad. These messages were developed using Self-Determination Theory. They encompass nine activity-based categories: (1) exceeding the daily activity goal; (2) meeting the daily target; (3) slightly below target; (4) low activity; (5) no activity data received; (6) improvement in activity compared with the prior day; (7) decrease in activity compared with the prior day; (8) three or more consecutive days of high activity; and (9) three or more consecutive days of low activity. Details of the development and validation of the motivated text messages have been published [38]. Message delivery will be dynamically tailored based on each participant’s recorded activity from the preceding day (e.g., exceeded goal, low activity, no data, or sustained inactivity). Messages will be brief, supportive, and action-oriented, serving as daily prompts to reinforce engagement and sustained physical activity.

Instructional education: Care recipients and care partners will be assigned six brief instructional videos (2–3 min each), organized into twice-weekly educational modules delivered over the three-week intervention period. Video engagement will be automatically tracked through the myACTIVEsteps platform. A video will be considered completed if at least 70% of the total viewing time is reached.

Virtual physical therapy: Care recipients and their care partners will have access to nine evidence-based video-guided physical rehabilitation modules over three weeks—three videos per week, each lasting 10–15 min. Duration of engagement and percent completion will be tracked remotely on the website. A video session will be considered completed if at least 70% of the total viewing time is reached. We expect both care partners and their care recipients to participate in each session. At the start of each session, the user ID of the person logging in will be required, and the person will attest that the care partner/care recipient is available during the session.

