### 2.10. Outcome Measures

Consistent with the study objectives, this pilot study includes two broad categories of outcomes: Feasibility Measures and Preliminary Efficacy Measures. The outcome variables, measurement metrics, and assessment time points are detailed below

Feasibility Outcome Measures:

The feasibility of the ACTIVE intervention will be evaluated in accordance with NIH guidelines for pilot studies [40], with a focus on recruitment, adoption, adherence, acceptability, fidelity, and retention (Table 3). Feasibility outcomes will be assessed separately by AD/ADRD status and by intervention and control arms.

Recruitment will be defined as the proportion of dyads recruited and randomized to the study, with a target of at least 75%. Adoption will be defined as the initial engagement in week one for smartwatch use, motivational text interaction, video-guided physical rehabilitation session initiation, and viewing educational videos, with a target of at least 75%. Adherence will be defined as sustained engagement during the three-week intervention period, with targets of at least 75% for days of smartwatch use, number of completed video-guided physical rehabilitation sessions, and number of educational videos viewed.

Acceptability will be assessed at weeks 5 and 9 using the System Usability Scale and the revised Technology Acceptance Model. The System Usability Scale is a 10-item survey (Cronbach alpha (α) = 0.90), and higher scores indicate higher usability of the specific study tool [49,50]. The revised Technology Acceptance Model is a 10-item scale (α = 0.89), and higher scores indicate greater acceptance of the specific technology [51,52]. The System Usability Scale and the revised Technology Acceptance Model surveys will be used to assess participants’ acceptability of (1.) the website (myACTIVEsteps.com), (2.) the Fitbit smartwatch, (3.) motivational texts, (4.) educational videos, and (5.) video-guided physical rehabilitation. Acceptability will be defined as a System Usability Scale score of at least 68 and a revised Technology Acceptance Model score of at least 4.0. [49,50,51,52]. Fidelity will measure the proportion of motivational and educational text notifications successfully delivered, with a target of at least 90%. Retention will be defined as the proportion of dyads that complete the study, with a target of at least 75%.

Preliminary Efficacy Outcome Measures:

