### 2.13. Analysis Plan

Handling of Missing Data: We anticipate low levels of missing data, which will be assessed for randomness using Little’s test [63,64]. Multiple imputation with chained equations will be used when appropriate [65,66,67], with sensitivity analyses to evaluate robustness of results. For feasibility outcomes, missing data will be minimized through proactive monitoring and participant reminders, and patterns will be summarized descriptively. For preliminary efficacy analyses, linear mixed-effects models will accommodate incomplete longitudinal data under an intention-to-treat framework. The percent and potential impact of missing data will be reported.

Feasibility Assessment: Six feasibility outcomes (recruitment, adoption, adherence, acceptability, fidelity, retention): will be summarized overall and stratified by AD/ADRD status (dyads with mild AD/ADRD and dyads without mild AD/ADRD) and by participant role within the dyad (care recipient vs. care partner). We will report the proportions and mean distributions, including 95% confidence intervals, for the feasibility measures, and descriptively compare these values with the preset benchmark (Table 3). A “go” decision will be made if the majority of benchmarks are met, a “conditional go” if some but not all benchmarks are achieved (with justification for modifications), and a “stop” decision if most benchmarks are not met. Feasibility outcomes will be assessed separately by AD/ADRD status and by intervention and control arms. Differences in feasibility outcomes by AD/ADRD status and by participant role will be explored descriptively using mean differences and differences in proportions with 95% confidence intervals.

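### The 0.66–0.84 precision statement in section 2.8 fits member-level proportions only; for retention, and for joint virtual-PT completion scored once per dyad or within one role, it is 0.63–0.87

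*Protocol article*

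**What the plan says.** Section 2.8 states its purpose as follows: "A sample of 50 dyads (n = 100) provides adequate precision to estimate key feasibility parameters that guide go/no-go decisions". The calculation starts from an example: "Using an expected proportion of 0.75 (e.g., completion of ≥75% of virtual PT modules), the unadjusted SE is 0.043". For clustering, "we assume an intra-cluster correlation (ICC) of 0.1–0.3, which is typical for partner dyads"; at a correlation of 0.2 and two people per cluster, "the design effect is 1.2, and the cluster-adjusted SE (Equation (3)) is 0.047". The result is "The cluster-adjusted 95% CI for a 75% completion rate (Equation (4)) is therefore 0.66–0.84".

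Other sections fix the unit on which the outcomes are counted:

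- Section 2.10: "Retention will be defined as the proportion of dyads that complete the study, with a target of at least 75" per cent. Section 2.6 adds that the whole dyad is withdrawn if either member stops.
- Section 2.5, on the video-guided sessions: at the start, "the user ID of the person logging in will be required, and the person will attest that the care partner/care recipient is available". Both members are expected to take part in every session.
- Section 2.13: "Feasibility outcomes will be assessed separately by AD/ADRD status and by intervention and control arms". The same section also calls for summaries by role within the dyad. Section 2.2 sets 25 dyads with and 25 without mild dementia.

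**The concern.** The interval in 2.8 treats the two members of a dyad as almost separate observations: a design effect of 1.2 leaves 100/1.2, or about 83, effective observations. That is reasonable where each member produces a separate, only weakly related value. It is not reasonable where both members necessarily share one value, because 50 dyads then carry 50 observations.

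Retention falls in the second group by definition. Virtual-PT completion, the outcome the interval is printed against, appears to fall there as well, because a session is done together and opened under one login.

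At stake is the only calculation offered in support of the sample size. A reader planning the larger trial would take the retention and PT estimates to be more precise than 50 dyads can make them. The gap matters most in the mild AD/ADRD stratum: the Discussion (section 3) treats adequate retention and adherence there as grounds for including this population in larger trials, yet no stratum precision is stated.

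**Working it through.** **Inputs.** Expected proportion p = 0.75, n = 100 members, cluster size m = 2, correlation 0.2 (range 0.1–0.3) and multiplier 1.96, all from section 2.8. 50 dyads, 25 per AD/ADRD stratum, from sections 2.2 and 2.8.

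**Formulas (those of section 2.8).** SE = √(p(1 − p)/n); design effect = 1 + (m − 1) × ICC; interval = p ± 1.96 × SE × √(design effect).

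**Step 1: reproduce the stated figure.**
- Unadjusted SE = √(0.75 × 0.25/100) = 0.0433.
- Design effect = 1 + 1 × 0.2 = 1.2; adjusted SE = 0.0433 × √1.2 = 0.0474.
- Half-width = 1.96 × 0.0474 = 0.093; interval 0.657–0.843, which rounds to the printed 0.66–0.84.
- Over the plan's own ICC range: 0.661–0.839 at 0.1 and 0.653–0.847 at 0.3. No value in that range comes near the dyad-level result below.

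**Step 2: retention, overall.**
- Both members always have the same value, so ICC = 1 and the design effect is 2. This is the same as n = 50.
- SE = √(0.1875/50) = 0.0612; half-width = 1.96 × 0.0612 = 0.120; interval 0.630–0.870.
- Ratio of half-widths = √(2/1.2) = 1.29, so 29% wider than stated.

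**Step 3: virtual-PT completion, by scoring rule.**
- Scored once per dyad: n = 50, interval 0.630–0.870.
- Each session credited to both members: identical values, ICC = 1, same interval.
- Scored within one role (care recipients only, or care partners only): 50 people, one per dyad, same interval.

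**Step 4: one AD/ADRD stratum (25 dyads, 50 members).**
- Dyad-level outcome: SE = √(0.1875/25) = 0.0866; half-width 0.170; interval 0.580–0.920.
- Member-level proportion at ICC 0.2: SE = √(0.1875/50) × √1.2 = 0.0671; half-width 0.131; interval 0.618–0.882. At ICC 0.1 and 0.3 it is 0.624–0.876 and 0.613–0.887.

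**The case against.** The strongest reply is that most benchmarks in Table 3 are not dyad-level. Each member wears a watch, both receive texts, care partners have their own parallel educational modules, and both complete the usability and acceptance surveys. For the proportions among these, 100 members with a modest design effect is a sound basis, and 0.66–0.84 stands for the pooled estimate. A reader might infer that every go/no-go outcome is dyad-level and that 0.63–0.87 should replace the printed interval throughout. The documents do not support that.

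Other parts of the reply also hold:

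- Section 2.5 does not say how a joint session is credited, so a single value per dyad is inferred from the login procedure. A reader might go further and suppose that scoring by login would give one member full credit and the other none. The article adopts no such rule.
- Recruitment is a dyad proportion, but its denominator cannot be the 50 dyads enrolled; it is a larger pool whose size is not given.
- Acceptability is judged on mean scores, so no interval for a proportion describes it.
- Section 2.8 also rests on cited recommendations for pilot sample sizes, so the interval is not the only justification for 50 dyads.
- The decision rule in section 2.13 counts benchmarks met and compares estimates descriptively. No confidence limit enters it, so the planning interval does not itself change a decision.

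None of this rescues 0.66–0.84 for retention, where the definition and the withdrawal rule leave no choice of unit, or for PT completion under joint or single-role scoring.

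**Conclusion.** Section 2.8 contains no arithmetic error; the fault is the unit of analysis. For retention the stated precision is too favourable: 0.63–0.87 rather than 0.66–0.84. The same holds for virtual-PT completion, conditional on scoring it once per dyad, crediting both members, or scoring within one role.

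The stratum figures need care. It is tempting to set 0.170 against 0.093 and to apply 0.58–0.92 to every outcome in a stratum. Much of that gap is simply the halving of the sample, section 2.8 claims no stratum precision, and 0.58–0.92 belongs only to dyad-level outcomes. Within a stratum the like-for-like comparison is 0.170 against 0.131, again about 29%.

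Assumptions: a true proportion of 0.75, the normal-approximation interval used in 2.8, PT completion read as a yes/no indicator as 2.8 does, 25 dyads in each stratum, and no dyad missing from the denominator.

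**What to change.** Restate section 2.8 by type of outcome:

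- Retention and joint virtual-PT completion: n = 50 dyads, SE 0.061, 95% CI 0.63–0.87.
- Pooled member-level proportions, such as smartwatch wear and educational-video viewing: keep 0.66–0.84.
- Per AD/ADRD stratum: 0.58–0.92 for dyad-level outcomes (25 dyads) and about 0.62–0.88 for member-level proportions (50 members, ICC 0.2).
- Recruitment: do not attach 0.63–0.87; base its precision on its own denominator once that is defined.
- Acceptability: do not attach an interval for a proportion.

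In section 2.5 or 2.10, state that each joint PT session is scored once per dyad.

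The cost is wording and a less favourable precision statement. Enrolment, design and benchmarks are unchanged.
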